# SWE and SMI ultrasound techniques for monitoring needling treatment of ankylosing spondylitis: study protocol for a single-blinded randomized controlled trial

**DOI:** 10.1186/s13063-021-05344-z

**Published:** 2021-06-07

**Keywords:** Acupuncture, Ankylosing spondylitis, Musculoskeletal ultrasound, Physical dysfunction, Randomized controlled trial

## Abstract

**Background:**

Ankylosing spondylitis (AS) is a high-incidence disease in young men that interferes with patients’ physical and mental wellbeing and overall quality of life (QoL). It is often accompanied by arthralgia, stiffness, and limited lumbar flexibility. Acupuncture is safe and effective for reducing the symptoms of AS, but the underlying mechanisms by which it does so are not fully understood. Therefore, to objectively assess acupuncture efficacy, which is critical for patients making informed decisions about appropriate treatments, we will use shear-wave elastography (SWE) and superb microvascular imaging (SMI) ultrasound techniques to evaluate elasticity of lumbar paraspinal muscles and blood flow to the sacroiliac joint (SIJ) in AS.

**Methods:**

We will recruit a total of 60 participants diagnosed with AS and 30 healthy subjects. Participants will be randomly allocated 1:1 to either an acupuncture group or a sham control acupuncture group. Primary-outcome measures will be musculoskeletal ultrasound, Ankylosing Spondylitis Quality of Life Scale (ASQoL), Bath Ankylosing Spondylitis Metrology Index (BASMI), and the Visual Analogue Scale (VAS) for pain. Secondary outcome measures will be the Bath Ankylosing Spondylitis Disease Activity Index (BASDAI), Bath Ankylosing Spondylitis Function Index (BASFI), and Fatigue Scale-14 (FS-14). We will monitor the effect of acupuncture or sham acupuncture on blood flow and SIJ inflammation using SMI, lumbar-muscle stiffness using SWE and the lumbar paraspinal-muscle cross-sectional area (CSA) using a two-dimensional (2D) grayscale imaging. QoL, physical function, and fatigue will be assessed using an evaluation scale or questionnaire developed for this study, with outcomes measured by the ASQoL, BASMI, BASDAI, BASFI, and FS-14. Healthy subjects will not receive acupuncture but undergo only musculoskeletal ultrasound at baseline. Acupuncture and sham control acupuncture interventions will be conducted for 30 min, 2–3 times/week for 12 weeks. Musculoskeletal ultrasound will be conducted at baseline and post-intervention, while other outcomes will be measured at baseline, 6 weeks, and post-intervention. The statistician, outcome assessor, and participants will be blinded to treatment allocation.

**Discussion:**

The results of this single-blinded, randomized trial with sham controls could help demonstrate the efficacy of acupuncture and clarify whether musculoskeletal ultrasound could be used to evaluate AS.

**Trial registration:**

ClinicalTrials.gov ChiCTR2000031476. Registered 3 April 2020.

## Background

Ankylosing spondylitis (AS) is a systemic disease characterized by chronic inflammation of the axial joint, involving the sacroiliac joint (SIJ), with primary clinical symptoms of arthralgia, stiffness, and limited flexibility [1]. Over the past 15years, the total prevalence of AS in the mainland China has been 0.29%, ranging from 0.42% in males to 0.15% in females [2]. The primary pathology includes inflammation of the bony attachments of tendons, ligaments, or joint capsules [3]. Physical dysfunction in AS can potentiate serious health conditions and lead to fatigue, depression, anxiety, and decreased quality of life (QoL) [4, 5]. The disease imposes substantial physical and social burdens on patients and can interfere with work and schooling [6, 7]. The goals of treatment are to alleviate symptoms, improve functioning, decrease disease complications, and forestall skeletal damage as much as possible [8]. The use of non-steroidal anti-inflammatory drugs (NSAIDs) and very expensive biologics is recommended for treatment [9]. However, due to the significant side effects [10], development of therapeutic resistance to drug treatment [11] and high drug costs, such use places a huge burden on patients. Thus, nonpharmacological intervention has become one of the most important options for AS [12]. Alternative therapies play an important role in treating this disease; for example, a combination of the Traditional Chinese Medicine (TCM) with, especially, acupuncture can achieve better effect.

Acupuncture is a safe alternative therapy with minimal side effects that has shown benefits in alleviating symptoms, reducing complications, and accelerating recovery in AS [13], and it has been shown to improve joint functional flexibility when used in the management of pain and rheumatic diseases [14–17]. Previous systematic studies support that acupuncture could be an option for treating AS [18, 19].

The 2019 guidelines of the American College of Rheumatology (ACR) [8] state that magnetic resonance imaging (MRI) is not suitable for detecting subclinical inflammation in patients with stable disease and recommend against patients obtaining spine radiographs at scheduled intervals to monitor progression, as the practice entails radiation exposure and will not lead to alteration of treatment in most cases. Therefore, it is particularly important to find a method that is safe and can be used at short intervals to detect subclinical inflammation in a timely manner. Ultrasound has become part of the fundamental Outcome Measures in Rheumatology (OMERACT) methodology validation by repeatedly exercises across various domains, including inflammatory burden and structural damage [20, 21]. Musculoskeletal ultrasound is a reliable evaluation method that directly visualizes characteristics of rheumatic conditions such as synovitis, tenosynovitis, bursitis, enthesitis, crystal depositions, bone erosions, or osteophytes/enthesophytes. It is more sensitive than X-ray or MRI in physical tendons, ligaments, or joint capsules [22, 23]. Early detection of subclinical lesions can help decision makers improve the quality of their daily clinical practice in rheumatic diseases.

Although musculoskeletal ultrasound is less sensitive than MRI and X-ray in early detection of synovitis and tenosynovitis [24], it is suitable for short-term evaluation of stable rheumatic diseases, offering highly accessible, low-cost, real-time imaging without radiation [25, 26]. The OMERACT Ultrasound Working Group has engaged in the validation of ultrasound as an outcome measurement instrument (OMI) by defining ultrasound manifestations of spondyloarthritis (SpA) [27].

This high-quality, randomized controlled trial (RCT) was designed via a pragmatic trial approach to objectively assess the efficacy of acupuncture using musculoskeletal ultrasound and a sham acupuncture group.

### Objectives

Our research hypotheses are as follows: (1) musculoskeletal ultrasound will be used as a short-term effective-examination method and objective auxiliary-examination method for AS. (2) Acupuncture will reduce subjective pain rating, improve joint functional flexibility, and the effect of pain on ASQoL.

## Methods/design

### Study setting

The study will follow the principles of the Consolidated Standards of Reporting Trials (CONSORT) for a two-arm randomized, superiority, parallel control clinical trial, as well as the Standards for Reporting Interventions in Clinical Trials of Acupuncture (STRICTA) statement for acupuncture [28, 29]. This will be a single-blinded RCT with a sample size based on published evidence in comparative studies. Sixty AS patients will be randomly established at a 1:1 ratio, including the acupuncture group and sham control acupuncture group. At the same time, thirty healthy volunteers will be recruited as blank control group. The sham control acupuncture group is set for placebo control to evaluate the clinical efficacy of acupuncture. AS patients blinded to study conditions. The study will be conducted at the Guangdong Provincial Hospital of Chinese Medicine (GPHCM), Department of Acupuncture, Guangdong, China, following the Standard Protocol Items: Recommendations for Interventional Trials (SPIRIT). For the participant timeline, see Fig. 1.

**Fig. 1 Fig1:**
[figure not shown]
SPIRIT figure for schedule of enrollment, interventions and assessments. ASQoL, Ankylosing Spondylitis Quality of Life; VAS, visual analog scale; BASMI, Bath Ankylosing Spondylitis Metrology Index; BASDAI, Bath Ankylosing Spondylitis Disease Activity Index; BASFI, Bath Ankylosing Spondylitis Functional Index; FS-14, Fatigue Scale-14.

### Recruitment

A total of 60 AS patients age 18–60 years and 30 healthy volunteers will be recruited for this study. AS participants will be recruited from both the outpatient and inpatient departments of the GPHCM, Department of Rheumatology. Study flyers, bulletin boards at the hospital, and online advertisements will also be used for patient recruitment. Healthy volunteers will be recruited from among students of the Guangzhou University of Chinese Medicine. Treatment and measurements will be performed at the GPHCM. Participants will contact the recruitment staff by telephone or WeChat. Recruitment staff will be responsible for the enrollment of participants. If they meet the study criteria, they will be invited to the Department of Acupuncture and Moxibustion, Guangdong Provincial Hospital of Chinese Medicine, to undergo the study. Eligible candidates will be asked to sign an informed consent form before intervention begins.

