### Inclusion criteria

Recruitment conditions are as follows: (1) a definite diagnosis of axial AS during a stable disease period; (2) 18–60 years of age, onset age <40 years; (3) currently being treated at a stable dose of medication for ≥4 weeks prior to randomization and have received no biologic therapy within the past 3 months; (4) course of disease ≤10 years; and (5) willingness to sign the informed-consent form. Potential participants who satisfy the inclusion criteria will be sent a more detailed information leaflet for informed consent. They will be contacted few days later to determine whether they are interested in participating, and, if so, an appointment will be made for them to visit the Guangdong Provincial Hospital of Chinese Medicine (GPHCM).

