### Data analysis

We will use SPSS software version 18.0 (IBM Corp, Armonk, New York, US) to perform data analysis. Demographic and baseline data will be analyzed with standard descriptive statistics. Data will be presented as the mean ± standard deviation (SD). Between-group differences will be tested using repeated-measure analyses of variance (ANOVAs). The entire data analysis process will be performed by statisticians who are independent from the research team and blinded to the group settings. The accepted level of significance for all analyses will be *P* < 0.05.

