## Discussion

The purpose of this trial is to assess the impact of acupuncture in the management of AS. It is clear that increased muscle stiffness is associated with poor range of motion [48], and a chronic inflammatory condition has significant impact on QoL. Patients report that back pain, arthralgia, and stiffness influence their daily work productivity and nocturnal sleep quality [49]. Acupuncture is used to reduce muscle stiffness and increase somatic activity in AS patients, and it is monitored by musculoskeletal-ultrasound techniques that, if less operator dependent, could obtain more-stable and reliable results [50]. The design of an appropriate control group for a clinical trial is critical. We will set a healthy-control group for baseline comparison, as there is currently no standardized for musculoskeletal-ultrasound measurement of AS. However, it is difficult to use placebo needles for controls. Therefore, we will use non-acupoints and superficial puncturing, which are considered ineffective, in the sham acupuncture group.

NSAIDs are often first-line treatment for AS, and biologics are the next step up. However, patients who have inadequate response to NSAIDs but cannot afford biologics often experience significant pain and impairment of their QoL [51]. This trial would provide evidence for acupuncture care for this group of patients.

Despite the measures taken to ensure a well-controlled trial, there are several methodological limitations to this study. The treatment intervention duration of 12 weeks might make it difficult to ensure patient compliance. Other aspects such as the trial results are meant to describe an approach to treatment for the typical patient and cannot anticipate all possibilities; clinicians must make careful clinical assessments based on sound clinical judgment of each patient’s circumstances and consideration of the patient’s preferences. In spite of its limitations, we hope that the trial will help provide new insights into the value of acupuncture and the evidence of musculoskeletal-ultrasound measures in AS.

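### Healthy volunteers come only from university students, so the baseline patient-versus-healthy ultrasound comparison mixes ankylosing spondylitis with age

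*Protocol article*

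**What the plan says.** The Recruitment section sets the group sizes and the patients' age range: "A total of 60 AS patients age 18–60 years and 30 healthy volunteers will be recruited for this study". No age range is attached to the volunteers. The same section names their only source: "Healthy volunteers will be recruited from among students of the Guangzhou University of Chinese Medicine".

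Inclusion criteria narrow the patient ages. Criterion 2 is "18–60 years of age, onset age <40 years" and criterion 4 is "course of disease ≤10 years".

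The Discussion states what the healthy group is for: "We will set a healthy-control group for baseline comparison, as there is currently no standardized for musculoskeletal-ultrasound measurement of AS". The Methods part of the Abstract limits what is done to them: "Healthy subjects will not receive acupuncture but undergo only musculoskeletal ultrasound at baseline".

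The Randomization section allocates participants to acupuncture or sham only, so the healthy group stands outside the randomisation.

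**The concern.** The healthy group exists to show what ultrasound measurements look like without the disease. A reference group does this only if it resembles the patients in other respects that may move the measurements. Muscle stiffness and muscle size may plausibly change with age. A student group is expected to be young and narrow in age, while the patients span roughly three decades.

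If age moves the measurement, a patient-student difference appears even where the disease has no effect. If age and disease act in opposite directions, a real disease difference can be hidden. In either case the 30 extra scans would not serve the purpose given in the Discussion. The recruitment source is a design decision fixed in this document, and an analysis plan cannot supply healthy measurements at ages where no healthy person was scanned.

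**Working it through.** The protocol gives no sample size, effect or power for patients versus healthy volunteers, so there is no figure of its own to reproduce. The check has four steps.

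**1. Effective patient age.** Onset is below 40 and the course is at most 10 years. If the course is counted from onset, age at entry is below 40 + 10 = 50. The upper part of the stated 18–60 range cannot then be filled.

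**2. Age gap and overlap.** These ages are assumptions, not figures from the documents: students uniform on 18–25, patients uniform on 18–50.
- Mean gap: (18 + 50)/2 − (18 + 25)/2 = 34 − 21.5 = 12.5 years.
- Share of patients older than any student: (50 − 25)/(50 − 18) = 25/32 = 78%.

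**3. False positives from a difference due to age alone.** Inputs from the protocol are 60 patients, 30 volunteers and a significance level of 0.05 (taken as two-sided, since the article does not say). In SD units, the standard error of the difference is √(1/60 + 1/30) = 0.224. A two-sample t-test with 88 degrees of freedom and noncentrality (difference)/0.224 gives:

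| Difference due to age alone (SD) | Noncentrality | Probability of P < 0.05 with no disease effect |
|---|---|---|
| 0 | 0 | 5% |
| 0.1 | 0.45 | 7% |
| 0.2 | 0.89 | 14% |
| 0.3 | 1.34 | 26% |
| 0.5 | 2.24 | 60% |

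**4. Link to an age slope, and what adjustment can do.** The slope is again an assumption. The table uses the 12.5-year gap and 3,000 simulated trials per slope, with zero disease effect.

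| Slope (SD per year) | Spurious difference (SD) | False positives, unadjusted | False positives, linear age adjustment |
|---|---|---|---|
| 0.01 | 0.12 | 7% | 4.3% |
| 0.02 | 0.25 | 19% | 4.6% |
| 0.03 | 0.38 | 37% | 4.6% |

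Adjustment restored the nominal rate because the simulated age effect was exactly linear. Even so, the variance of the patient-healthy contrast rose to about 1.6 times its unadjusted value. In real data the shape of the age effect in healthy people beyond student age could not be checked, because none would have been scanned.

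**The case against.** Several objections have weight.

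- **The stated range to 60 overstates the contrast.** This stands. The usable upper limit is about 50. The Abstract also describes the disease as one of young men, so enrolled patients may cluster at younger ages than a uniform spread. Both reduce the gap, but neither gives a reason to expect it to vanish against a student group.
- **The analysis plan, not shown, may adjust for age.** It may, and the Other outcomes section does collect age. This answers the point only within the ages the two groups share.
- **The size is unanchored.** This stands. Student ages, the age gap and the age slope are all assumed. At 0.1 SD the error rate is about 7%, close to nominal.

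A reader might also infer stronger claims that the documents do not support.

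- **That hypothesis 1 rests on this comparison.** The Objectives say only that "musculoskeletal ultrasound will be used as a short-term effective-examination method and objective auxiliary-examination method for AS", with no mention of healthy controls. That hypothesis can draw on patients' change from baseline to week 12.
- **That sex and body build are confounded too.** The Background gives a higher prevalence in men, but nothing is said about the sex mix or build of the volunteers. Silence in a condensed article is not an error.
- **That repeated-measures ANOVA will be misapplied to a group scanned once.** The test for the baseline contrast is a detail commonly left to the analysis plan.
- **That these volunteers are the only possible norm.** The Discussion says there is no standard for ultrasound measurement of this disease. It does not say that no healthy reference values exist.
- **That blood flow is certainly affected.** The Primary outcomes section describes the microvascular test in patients only, so it is unclear whether volunteers have it. Stiffness and muscle size are enough for the point.

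**Conclusion.** The point holds in a limited form. Student-only recruitment builds an age difference into the non-randomised baseline comparison of patients with healthy volunteers, and leaves little overlap for adjustment to use. That conclusion needs only the recruitment source, the patient criteria and the ordinary expectation that students are mostly young.

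The size of the bias cannot be determined from the documents. The range of about 7% to 60% false positives, for differences of 0.1 to 0.5 SD due to age alone at 60 versus 30, is an illustration and not an estimate.

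The randomised acupuncture-versus-sham comparison and within-patient ultrasound change are untouched. This is therefore a worthwhile, inexpensive improvement to an ancillary comparison and not a threat to the trial's main result.

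**What to change.** Keep 30 healthy volunteers and the single baseline scan, but recruit them frequency-matched to the enrolled patients on age band and sex, from hospital staff or the community as well as students. Compare at baseline with adjustment for age. Matching on sex is added because it costs almost nothing once age bands are in place, not because an imbalance has been shown.

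The Trial status section reports that recruitment is open, so some students may already be enrolled. In that case, fill the remaining places from the older age bands, restrict the patient-healthy comparison to the age range both groups cover, and label it descriptive.

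The cost is slightly slower volunteer recruitment or, under the fallback, fewer patients in the restricted comparison. How many depends on how many students have already been scanned, which the article does not say.

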### Inclusion criteria

Recruitment conditions are as follows: (1) a definite diagnosis of axial AS during a stable disease period; (2) 18–60 years of age, onset age <40 years; (3) currently being treated at a stable dose of medication for ≥4 weeks prior to randomization and have received no biologic therapy within the past 3 months; (4) course of disease ≤10 years; and (5) willingness to sign the informed-consent form. Potential participants who satisfy the inclusion criteria will be sent a more detailed information leaflet for informed consent. They will be contacted few days later to determine whether they are interested in participating, and, if so, an appointment will be made for them to visit the Guangdong Provincial Hospital of Chinese Medicine (GPHCM).

### Exclusion criteria

Potential participants will be excluded for the following reasons: (1) clinically important fracture of the spine; (2) spinal deformity or disability; (3) blood coagulation disorder; (4) presence of viral hepatitis, human immunodeficiency virus (HIV), or other blood infection; (5) pregnancy or lactation; (6) previous history of stroke or transient ischemic attacks; (7) pacemaker or other electrical device implanted; or (8) lack of consent, active pursuit of compensation or with pending litigation.

### Dropout criteria

Patients who have severe adverse reactions after acupuncture and cannot successfully complete the course of treatment;The participant was unable to follow the protocol treatment for personal reasons during the course or use other traditional Chinese medicine therapies.

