### Adverse events

Common treatment-related adverse events include dizziness, local subcutaneous hematoma, continuous post-needling pain, localized infections, and palpitations. Adverse events data will document the occurrence, duration, and severity of adverse reactions (symptoms and signs), and how the event was resolved (or not) during the treatment. Adverse events will be categorized by acupuncturists and related specialists as treatment-related or not within 24h after occurrence. If a participant reports a severe adverse event, it should be reported to principal investigators and the Institutional Ethics Committee (IEC) of Guangdong Provincial Hospital of Chinese Medicine, and they will decide to unblind and withdraw from the study. According to the situation, they will be referred to the emergency department or receive appropriate treatment. We will collect, assess, and report any spontaneously described adverse events from participants.

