### Sample size

The required sample size for this study was estimated based on a study by You et al. [47]: at the week 24, pain VAS score was 3.87±1.54 (mean ± standard deviation [SD]) in needle-knife group and 4.59±1.57 in the control group. With a conservative estimate of 0.36point difference on a 10-point VAS score between the two arms, and assuming a standard deviation of 0.72 for both arms, based upon a two sample t tests assuming equal variance analysis conducted by an independent statistician via PASS 15.0, a sample size of 23 per group will yield a power of 90% at an alpha (α) value of 0.05. To account for an anticipated dropout rate of 20%, finally, the sample size was inflated to 60 with 30 patients per arm will be sufficient to detect a clinically important difference in this trial.

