### Ethics and dissemination

All candidates who agree to participate and who meet all of the inclusion criteria and none of the exclusion criteria will be provided informed consent to obtain full understanding of what study participation will entail and the potential risks. Participants have the right to discontinue participation at any time. Data will be used in the aggregate only, and no identifying characteristics of individuals will be published or presented. On the consent form, participants will be asked if they agree to use of their data should they choose to withdraw from the trial. Participants will also be asked for permission for the research team to share relevant data with people from the regulatory authorities, where relevant. This trial does not involve collecting biological specimens for storage.

The study conforms to the principles of the Declaration of Helsinki. Ethical approval has been obtained from the IEC of the Guangdong Provincial Hospital of Chinese Medicine (YF2019-232-01). The trial protocol has been registered at the Chinese Clinical Trial Registry (ChiCTR2000031476). Results will be disseminated through journal articles, a master’s thesis, or conference presentations. Data will be used in the aggregate only, and no identifying characteristics of individuals will be published or presented.

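### Dropout defined by treatment events, combined with repeated-measures ANOVA, risks a completer comparison

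*Protocol article*

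**What the plan says.** The article's Dropout criteria give two routes. The first is "Patients who have severe adverse reactions after acupuncture and cannot successfully complete the course of treatment". The second is "The participant was unable to follow the protocol treatment for personal reasons during the course or use other traditional Chinese medicine therapies". Both describe what happens to treatment after randomisation. Neither mentions loss of contact or withdrawal of consent.

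Under Adverse events, a severe event is referred to the principal investigators and the ethics committee, and "they will decide to unblind and withdraw from the study".

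Under Sample size, 23 per group is raised to 30 per arm: "To account for an anticipated dropout rate of 20" per cent.

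Under Data analysis, one between-group method is named: "Between-group differences will be tested using repeated-measure analyses of variance (ANOVAs". The software line reads "We will use SPSS software version 18.0".

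On data from people who leave, Ethics and dissemination says that "participants will be asked if they agree to use of their data should they choose to withdraw from the trial".

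On visits, the abstract says that "other outcomes will be measured at baseline, 6 weeks, and post-intervention". Primary outcomes puts ultrasound at baseline and week 12 only.

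**The concern.** A patient who stops sessions or tries another TCM therapy can usually still give a week-12 pain score. Calling that patient a dropout merges two different things: stopping the allocated treatment and leaving the study. If assessment ends at that point, the final visit is missing. Classical repeated-measures ANOVA (the SPSS general linear model form) then deletes the patient listwise, including any week-6 value already collected.

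Removal may not be random. The active arm receives current at the maximum tolerated level (0.9–3.0 mA) and the sham arm 0.1–0.3 mA, so intolerance could differ by arm. Patients without relief may have more reason to seek other TCM care, and they are recruited at a TCM hospital. The Discussion itself expects compliance over 12 weeks to be difficult. If removal depends on arm and outcome, the groups compared at the end are no longer the groups that were randomised.

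**Working it through.** **Inputs.**
- Sample size section: 23 per group, 20% dropout, 30 per arm, planned VAS difference 0.36, SD 0.72.
- Cited study, same section: 3.87 ± 1.54 and 4.59 ± 1.57. Difference 4.59 − 3.87 = 0.72; average SD (1.54 + 1.57)/2 = 1.555.
- Assumptions, not in the article: the share removed in each arm, and how far removed patients differ from the rest.

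**Step 1: the plan's dropout allowance.** 23/(1 − 0.20) = 28.75, so 29; the plan rounds to 30. Conversely, 30 × 0.80 = 24 per arm remain. This step reproduces. The 23 itself does not follow from 0.36 and 0.72 (a two-sided t test needs 86 per group for 90% power; 23 fits a difference of 0.72 with SD 0.72). That is a separate matter, but it makes 0.36 an uncertain yardstick.

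**Step 2: what listwise deletion loses.** A patient with scale scores at baseline and week 6 but not week 12 holds two of three values and contributes none. For ultrasound, the same patient has no post-baseline value at all.

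**Step 3: selection in one arm.** Let m be the mean of the whole arm, d the share removed, S the SD, and x the number of SDs by which removed patients would have scored worse than m. The mean of those who remain is [m − d(m + xS)]/(1 − d) = m − [d/(1 − d)]xS. With d = 0.20 the shift is 0.25xS.

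| S | x = 0.5 | x = 1 | Difference paired with this S | Shift as share of it |
|---|---|---|---|---|
| 0.72 (protocol) | 0.09 | 0.18 | 0.36 (planned) | 25% to 50% |
| 1.555 (cited study) | 0.19 | 0.39 | 0.72 (observed) | 27% to 54% |

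If x is measured from the mean of the completers instead of the whole arm, the shift is dxS = 0.20xS: 0.07 to 0.14 at S = 0.72, and 0.16 to 0.31 at S = 1.555.

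**Step 4: losses in both arms.** With g the VAS gap between removed patients and completers, the net shift is the difference between the arms in d × g.
- Same d and same g in both arms: zero.
- 30% against 10%, with equal gaps of 0.36 to 1.44: (0.30 − 0.10) × g = 0.07 to 0.29.
- 10% against 30%: the same size with the opposite sign.

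Losing poor responders from the acupuncture arm flatters acupuncture; losing them from the sham arm flatters sham. The article gives nothing that fixes the direction.

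**The case against.** The strongest reply is that nothing in the article says dropouts leave the analysis. The Dropout criteria say who counts as a dropout, not that assessment ends. Data analysis states no exclusion, and imputation could precede the ANOVA. The analysis set and missing-data rule usually sit in the SAP or full protocol, which are not shown, so their absence is no fault. The consent form foresees use of withdrawn patients' data. A 20% inflation is routine. Withdrawal after a severe event is decided case by case, and only reactions that are severe and prevent completion count. Patients are blinded, which may reduce arm-dependent dropout.

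All of that stands against the reading that the plan is a biased completer analysis. A reader might infer this, but the documents do not support it as fact. A reader might also infer that the bias can match the planned effect, by setting 0.39 beside 0.36. That comparison mixes the cited study's SD with a difference the protocol pairs with SD 0.72.

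The reply does not remove the point. The dropout definition and the ANOVA are stated choices. The consent question concerns people who choose to withdraw and the use of their data; it does not provide for continued assessment after a protocol-defined dropout. A week-6 value kept on that basis would still be lost under listwise deletion. A later analysis plan cannot recover outcomes that were never collected.

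**Conclusion.** The point holds as a risk. Treatment-related dropout rules, an anticipated 20% loss and a method that in its classical form needs every visit together expose the trial to a completer comparison. This goes beyond a missing intention-to-treat statement, because a better and cheap alternative to the stated method exists.

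On the protocol's own SD, one-sided selection of 20% shifts the VAS difference by 0.09 to 0.18 points, a quarter to a half of the planned 0.36. On the cited study's SD it is 0.19 to 0.39, about 27% to 54% of that study's observed 0.72. Both ranges rest on an assumed gap of 0.5 to 1 SD from the arm mean and no selection in the other arm. The bias is zero with equal losses and equal gaps, and its direction is unknown. The wording should be corrected and the method changed; confidence is medium, because what happens to a dropout's later assessments is not stated.

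**What to change.** - Leave the rules for stopping treatment unchanged. Define stopping treatment and leaving the study separately, and keep the second for withdrawal of consent or loss of contact.
- State that VAS, ASQoL, BASMI and ultrasound continue at the scheduled visits after treatment stops, unless consent is withdrawn. This matters most for ultrasound: with a single post-baseline visit, no model can replace a missing week-12 value from an earlier one.
- Replace the repeated-measures ANOVA with a likelihood-based mixed model on all randomised patients in their allocated arm, using all available visits. It relies on data being missing at random, which is why continued collection comes first.
- Report the completer analysis as sensitivity only, with dropout counts and reasons by arm.

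The cost is protocol and SAP wording and a few extra contacts at visits already scheduled. A small downside is that data collected after other therapies may dilute the estimated effect.
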